### Procedure

Patients were invited to attend an information meeting, where members of the research group explained the purpose of the study in detail and handed out written information. To minimize dropout, the recruitment took place a maximum of two weeks ahead of the trial. A member of the research group visited the treatment center 1 week before the study to answer questions.

After giving informed consent, eligible participants were gathered to perform the interventions and assessments. These sessions were undertaken on-site at the clinics starting at 9:30 AM on Monday, Wednesday, and Friday within one week. The participants were asked to refrain from doing exercise on the days of the trial and on the days in between the interventions to give a 1-day washout period between the sessions. All sessions lasted 45 minutes. During the week of the trial, all participants received treatment as usual between the sessions.

The following exercise activities and control condition were tested in random order: (1) indoor soccer, (2) circuit training in a gymnasium using body weight, and (3) the control condition, attending a lecture on exercise and mental health.

Across all trial days, the participants were advised to eat breakfast about an hour before starting the trial. They were advised to have a light meal or snack after training, have lunch on all trial days, and keep hydrated throughout the day. Participants were also asked to limit the use of caffeine and nicotine during the test period. The flow of participants through the trial is shown in Figure 1.

**Figure 1 figure1:**
[figure not shown]
Flow of participants through the study. SUD: substance use disorder.

### Exclusion Criteria

Patients admitted to the treatment centers typically have comorbid ICD-10 mental disorders. None of these served as exclusion criteria as long as the participant was able to give informed consent. All patients at the clinics were invited to join; the only exclusion criterion was having a physical condition or injury that would impede physical activity participation. Some patients relapsed to substances during treatment. Patients who were suspected to be under the influence of drugs were asked to discontinue.

### Measures

#### Background Information

Therapists collected background information about the participants during an interview. The therapists filled in a questionnaire covering sociodemographic and treatment-related variables, ICD-10 substance use and mental disorders diagnosed during treatment, duration of problematic drug use, treatment history, level of activity before admission, and attitude toward physical activity. Height and weight were recorded. For most participants, this was based on measures taken at the treatment centers. A minority were self-reported.

#### Baseline and Follow-up Assessments

Mood (primary outcome), craving, affect, self-esteem, and state anxiety were measured with self-report questionnaires. The same questionnaires were repeated for baseline and follow-up assessments. The questionnaires chosen could be completed in 5 minutes, were amenable to repeated administration, and had sound psychometric properties.

The self-report questionnaires and saliva samples collected immediately before the sessions were the baseline assessment. Following the sessions, participants filled in self-report questionnaires on 4 occasions: immediately after the session and 1, 2, and 4 hours after the session. Immediately after the exercise sessions, participants were also asked to rate the perceived intensity. A saliva sample was gathered 4 hours after all sessions. Figure 2 illustrates the SPIRIT figure, study measures, and assessment time points.

Self-report measures were (1) the Feeling Scale, (2) drug craving, (3) the Positive and Negative Affect Schedule (PANAS), (4) the Rosenberg Self-Esteem Scale, (5) state anxiety, and (6) the Borg Rating of Perceived Exertion (RPE) scale.

First, changes in mood related to exercise were assessed with the Feeling Scale [39] (primary outcome), a single-item Likert scale ranging from –5 (very bad) to 5 (very good). Participants were instructed to indicate how they felt “at this moment.” The scale has been used extensively in acute exercise studies [40].

Second, drug craving was assessed using a single-item visual analog scale (VAS) ranging from 0 (no craving for drugs) to 10 (strong craving for drugs). Participants were instructed to indicate how strong their craving for drugs felt “at this moment.” The instrument has been used in previous studies of acute exercise [41] and it was tested in our recent pilot study [36], where it was shown to be sensitive to change.

Third, the PANAS assesses 2 dimensions of affect [42]. Participants self-rate 20 items on a 5-point Likert scale ranging from 1 (very slightly/not at all) to 5 (extremely). Ten of the items represent positive affect and the others represent negative affect.

Fourth, self-esteem was measured using the 10-item Rosenberg Self-Esteem Scale [43], which measures global feelings about oneself (that is, both positive and negative feelings). All items are answered using a 4-point Likert scale ranging from strongly agree to strongly disagree.

Fifth, state anxiety was assessed by a single-item VAS-scale ranging from 0 (no anxiety) to 10 (intensive anxiety/full panic).

Sixth, the Borg RPE scale [44] was administered 5 minutes after each exercise session to assess how strenuous the exercises were perceived by participants. The single-item scale ranges from 6 (no exertion at all) to 20 (maximal exertion).

**Figure 2 figure2:**
[figure not shown]
SPIRIT figure, study measures, and assessment time points. FS: Feeling Scale; HR: heart rate; PANAS: Positive and Negative Affect Schedule; RCT: randomized controlled trial; RPE: Rating of Perceived Exertion; RSES: Rosenberg Self-Esteem Scale; VAS: visual analog scale.

#### Device-Based Assessment of Physical Activity

In addition to collecting self-reports on how strenuous the exercises were perceived to be, data on the average and maximum heart rate were collected using a heart rate monitor (Polar M200; Polar Electro Ltd) during all of the conditions.

#### Biomarkers

Cortisol level was measured immediately before and 4 hours after the interventions. Saliva samples were collected using cotton swabs (Salivette; Sarstedt Inc). Collected samples were stored in a freezer until the end of the study. The cortisol level in saliva will be measured by liquid chromatographic–tandem mass spectrometry. The analyses will be performed at the Hormone Laboratory at Oslo University Hospital.

Consistent with Salivette recommendations, participants were asked not to eat or drink, use tobacco, or brush their teeth 60 minutes before the saliva samples were taken.

### Exercise Interventions

The aerobic and anaerobic exercises included in the study were chosen on the basis of participant feedback given during the pilot study. All exercise sessions were supervised by a qualified staff member, a nurse with formal education in physical activity for people with mental health and addiction disorders.

#### Soccer

Soccer was played with 5 participants on each team, including the goalkeeper. It was arranged in gyms that the treatment centers normally use for physical activity sessions. The participants were randomly divided into 2 teams. If fewer than 10 patients participated in the study at one site, staff from that treatment center were asked to join. The field was 20 × 40 m and the goal was 3 × 2 m.

Participants were asked to play a friendly match where goals were counted. They were told their soccer competency was not important and that all participation in the match was valuable for the team, and they were asked to try to give it their best. The match lasted for 45 minutes, with a 2-minute break after 15 and 30 minutes.

#### Circuit Training

Circuit training was performed in the same gymnasium as the soccer intervention. Due to the low cost and limited need for equipment, we used body weight exercises only. Participants completed 4 circuits consisting of 8 individual exercise stations. They spent 40 seconds exercising at each station, then 20 seconds resting before transitioning to the next station. Between each circuit there was a 2-minute rest. As participants were new to the training environment, the first circuit took slightly longer to complete. Thus, the average duration of training for most participants was 45 minutes (42-48 minutes). The 8 exercises were air squats, inch worms, bench dips, frog jumps, sit-ups, push-ups, walking lunges, and back extensions.

During the first circuit, participants performed the exercises together to make sure they did them correctly. This circuit functioned as a warm-up and was undertaken at lower intensity. If a participant had a physical disability or was restricted from performing an exercise, an alternative or adjusted exercise was substituted. Participants were asked to give their best effort at each station and to perform as many repetitions as they could within 40 seconds. They were also told that if the exercises felt easy, they should try to increase the number of repetitions, whereas if they felt they were too strenuous, they could decrease the number.

### Control Condition

Participants attended a 45-minute lecture with a PowerPoint (Microsoft Corp) presentation on the benefits of physical activity for physical and mental health. The lecture format was similar to what the patients would normally receive during conventional treatment. The lecture was given by a member of the research group in a meeting room at the treatment centers.

### Adherence

A member of the research group was on-site during the interventions to remind participants about the assessment times and to motivate them to participate in the conditions. The same staff member was also available to answer any questions about the questionnaires.

### Statistical Analyses and Power Calculation

Statistical power was estimated using G*Power (version 3.1.9.7; Heinrich-Heine-Universität Düsseldorf). Parameters were based on results from our feasibility study [36] and also took into account previous studies demonstrating medium effect sizes for acute exercise on mood states [38,45]. Assuming an effect size of 0.3 and power (β) of .8, with 3 groups and 5 measurement points, we estimate needing at least 21 participants to test our hypotheses. We planned to include one group of 5 to 10 participants from each site, which would give us 20 to 40 participants. Due to the experimental study design and the inclusion of only inpatients, we anticipate minimal missing data. Descriptive data will be calculated for each measure. Changes over time will be assessed using mixed (group × time) repeated-measures analysis of variance with post hoc contrasts. If participants return questionnaires with missing data, the missing items will be imputed using the last observation carried forward method. If questionnaires are returned with more than 50% of data missing, the questionnaire will be excluded from the analysis.

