### Setting and Participants

Inpatients from 4 treatment facilities were invited to participate. The main site for the study was the Department of Addiction Treatment - Adult, Division of Mental Health and Addiction, Oslo University Hospital. In addition, 3 other treatment centers were asked to participate (2 accepted): the Department of Addiction Treatment - Youth, Oslo University Hospital; an inpatient treatment center at the Division of Mental Health and Addiction, Vestfold Hospital Trust; and the Blue Cross Treatment Center, Slemdal, Oslo. The study was conducted in a clinical setting, where the participants received treatment.

The treatment centers are staffed by medical doctors, nurses, psychologists, and social workers. Treatment includes individual and group counseling and pharmacotherapy. Patients participate in structured group sessions and practice activities of daily living, including routines for house cleaning, eating, and sleeping. They receive individual sessions with psychologists, doctors, and social workers and participate in team meetings and social training. Physical exercise, including strength training, ball games, walks, and running, are part of the usual treatment program. Before admission to treatment, all patients complete detoxification.

Recruitment took place at the treatment centers, where patients were given information and invited to participate in the study by members of the research group and a local project coordinator. All participants were diagnosed with a SUD based on the International Classification of Diseases, Tenth Revision (ICD-10), were inpatients at one of the treatment centers, and were 18 years or older.

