### Study Design and Randomization

This study is a short-term, multicenter randomized controlled trial with a single pretest and multiple posttests. Using a crossover design, changes in mood, craving, state anxiety, affect, and self-esteem were assessed by comparing the initial measurement (taken immediately before exercise) with 4 follow-up assessments, first immediately after exercise, then at 1, 2, and 4 hours postintervention. The design allows the pattern of change over time to be seen.

Participants completed 3 sessions—2 supervised group exercise sessions (soccer and circuit training) and 1 control condition (attending a lecture about the health benefits of physical activity)—within the same week. All the sessions were performed in a group setting.

The order of the study conditions was determined by a random number generator and placed in sealed envelopes at a site separate from the study location. When a group of suitable patients (5-10 patients) was recruited at a site, a sealed envelope with the order of exercise and control conditions was drawn by a person outside of the research group.

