## Results

Data collection was completed in August 2019. In total, 39 patients admitted at 3 treatment centers participated in the study. Data will be analyzed during 2020.

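### The requirement of 21 participants is calculated for three independent groups, so its 80% power does not describe this group-randomised crossover

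*Protocol article*

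**What the plan says.** The section Statistical Analyses and Power Calculation reports a G*Power estimate that assumes "an effect size of 0.3 and power (β) of .8, with 3 groups and 5 measurement points, we estimate needing at least 21 participants". The analysis named there matches it: "Changes over time will be assessed using mixed (group × time) repeated-measures analysis of variance with post hoc contrasts". On recruitment the section says: "We planned to include one group of 5 to 10 participants from each site, which would give us 20 to 40 participants".

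Study Design and Randomization describes something different. "Using a crossover design, changes in mood, craving, state anxiety, affect, and self-esteem were assessed", and "Participants completed 3 sessions—2 supervised group exercise sessions (soccer and circuit training) and 1 control condition". One sealed envelope fixes the order of conditions for each recruited group of 5 to 10 patients, and all sessions are held in groups.

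Four facilities were invited. Setting and Participants says that, besides the main site, "3 other treatment centers were asked to participate (2 accepted". The Results section confirms this: "In total, 39 patients admitted at 3 treatment centers participated in the study".

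**The concern.** The power statement counts three groups, but the design has three conditions and one set of people. Condition is a within-person factor, and what is randomised is a recruited group rather than a person. Nothing in the calculation reflects either feature.

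The article offers 21 as enough to test its hypotheses. Those compare exercise with the lecture, and a separate research question compares soccer with circuit training. Both are contrasts between conditions, and an omnibus interaction does not give their power. A reader who sees 39 enrolled against 21 required may assume that both comparisons are well powered, and may then read a null soccer-versus-circuit result as evidence of no difference.

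**Working it through.** **Inputs from the article:** effect size 0.3, power 0.80, 3 groups, 5 measurement points, N at least 21, 39 enrolled at 3 sites, groups of 5 to 10.

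**Assumed, because not stated:** effect size read as Cohen's f, alpha 0.05, correlation between repeated measures ρ = 0.5, sphericity ε = 1. Intraclass correlations (ICC) are shown as a range.

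**1. Reproducing 21.** For the within-between interaction with k = 3 independent groups and m = 5 times:
- noncentrality λ = f²·N·m/(1 − ρ) = 0.09 × N × 5/0.5 = 0.9N
- df1 = (k − 1)(m − 1) = 8
- df2 = (N − k)(m − 1) = 4(N − 3)

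| N | λ | df2 | Power |
|---|---|---|---|
| 18 | 16.2 | 60 | 0.776 |
| 19 | 17.1 | 64 | 0.806 |
| 20 | 18.0 | 68 | 0.832 |
| 21 | 18.9 | 72 | 0.856 |

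The bare minimum is 19. Rounding up to three equal groups gives 3 × 7 = 21, the stated figure. With the same settings the time main effect needs 15 and the between-group main effect needs 69. A time main effect with ρ = 0.3 also gives 21, but it too has three independent groups.

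**2. Sensitivity of that formula.** At N = 21, power is 0.69 with ρ = 0.3 and 0.62 with ε = 0.5. At the enrolled N = 39 the same two cases give 0.96 and 0.92.

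**3. Condition as a within-person factor, no clustering.** With 3 × 5 cells per person and the same f carried over:
- λ = f²·N·15/(1 − ρ) = 2.7N
- df = 8 and 8(N − 1)

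Power is 0.83 at N = 7 and above 0.99 at N = 21. Over ρ from 0 to 0.7 the required N runs from 13 down to 5. Pairing alone therefore makes 21 conservative for the omnibus test.

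**4. The same test with group allocation.** For 3 groups of 7, divide λ by 1 + (7 − 1)·ICC and use error df 8(3 − 1) = 16. Power is 0.98, 0.95, 0.85 and 0.73 at group-by-condition ICC 0.05, 0.10, 0.20 and 0.30.

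**5. A single paired contrast.** A paired t test at 80% power that ignores clustering detects 0.64 SD of the within-person difference with 21 people and 0.46 SD with 39.

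For 39 people in G equal groups of size n = 39/G, take the design effect D = 1 + (n − 1)·ICC, noncentrality δ√(39/D), and G − 1 degrees of freedom. For G = 4 (n = 9.75), ICC 0.05 gives D = 1.44 and an effective size of 27; ICC 0.10 gives D = 1.88 and 21.

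| Groups | Detectable at ICC 0.05 | Detectable at ICC 0.10 |
|---|---|---|
| 4 | 0.82 SD | 0.93 SD |
| 5 | 0.70 SD | 0.78 SD |
| 6 | 0.64 SD | 0.70 SD |

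**6. Recruitment.** The four-site plan is 4 × 5 = 20 to 4 × 10 = 40, as stated. For the three sites that took part, one group each gives 3 × 5 = 15 to 3 × 10 = 30. Since 39/10 = 3.9, the 39 participants formed at least 4 groups if the limit of 10 held. The article does not give the number.

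**The case against.** The strongest reply is that nothing is miscalculated. The figure reproduces, it matches the interaction analysis that the article names, and the contrasts are labelled post hoc. A condensed article may leave alpha, correlation and sphericity to the full protocol. All of that stands. The reproduction depends on settings that are not printed, and three groups of 7 is an inference from the wording and the match. What remains is a conflict within the article itself: three groups in one section, and one set of participants taking all three conditions in another.

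A reader might go further and infer that the trial is underpowered. The documents do not support that. Pairing raises the power of the omnibus test, 39 people were enrolled, and the loss of power in step 2 largely disappears at that number. Only an assumed ICC and number of groups pull power down, and the article gives neither.

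A reader might also take 0.3 as a standardised paired difference, which would make the trial look weak. That does not fit a G*Power calculation with groups and measurement points, and 21 reproduces with 0.3 as f.

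On recruitment, 20 to 40 is right for the four sites planned. The lower end of 20 falls below 21, but the same formula still gives 83% there, so this has no practical consequence.

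**Conclusion.** The point holds as a mismatch between the power model and the design. The 80% figure describes a parallel comparison of three independent groups, not a crossover with group-level allocation, and it does not give the power of either contrast of interest.

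The size and sign of the discrepancy cannot be fixed from the article. For the omnibus test without clustering, 21 is about three times the 7 needed at ρ = 0.5. For one contrast with 39 people, the detectable difference is 0.46 SD of the within-person difference if clustering is ignored. It is 0.64 to 0.93 SD for 4 to 6 groups at ICC 0.05 to 0.10. Those clustered figures rest on an assumed ICC, equal group sizes and an assumed number of groups, so they illustrate the issue and do not estimate this trial's power.

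A smaller point also stands: 39 participants at 3 sites do not fit one group of 5 to 10 per site, so the number of randomised units is unknown to the reader.

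**What to change.** Replace the sample-size sentence with the precision of the actual design. For the 39 participants, give the detectable exercise-versus-lecture and soccer-versus-circuit differences on the Feeling Scale, with condition as a within-person factor and the actual number of randomised groups. State the effect-size metric, alpha, correlation and sphericity assumptions, and show a range of group-by-condition ICC (0 to 0.10, for example, as a declared assumption).

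Keep 20 to 40 as the four-site plan, and add that 3 sites took part and how many groups the 39 formed. Report soccer versus circuit training as an estimate with a confidence interval, so that a null test is not read as equivalence.

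The cost is text and a short recalculation. No extra enrolment is needed, and the article says the data were still to be analysed.

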## Introduction

Substance use disorders (SUD) have wide-reaching impacts on health and well-being and contribute substantially to the global disease burden [1]. They are associated with shorter life expectancy, and comorbid medical conditions are common [2]. The prevalence of co-occurring personality and other psychiatric disorders is high, with estimates ranging from 50% to 90% [3]. Mood and anxiety disorders are prevalent and affect both the severity and outcome of treatment [4]. Current treatment options for SUDs include cognitive behavioral therapy, motivational interviewing, and medication. Although documented as effective, these methods do not help all patients. Relapse rates range between 40% and 60% [5], and dropout rates from in-patient treatment is around 30% [6].

Despite their high prevalence, few people with SUDs ever receive treatment, and there is a need for more treatment options [7,8]. One potential explanation for poor help seeking is the perceived stigma associated with traditional treatments [9,10]. Lifestyle-focused interventions have potential to increase help seeking by reducing this stigma.

Physical activity has been suggested as an alternative or complementary treatment option for SUDs [11-13]. The rationale is that physical exercise might be effective due to its beneficial effects on factors related to relapse and the maintenance of the disorder, such as comorbid mental disorders, craving, and emotional dysregulation [14-17].

Regular physical activity increases fitness and lowers the probability of chronic diseases [18,19]. It has been proposed as a strategy for alleviating symptoms of psychiatric disorders in general [20,21], and its application in the mental health care system is increasing. Regular physical activity has been shown to be effective in the prevention and treatment of common mental health conditions [22]. Studies also indicate that physical activity alleviates symptoms in people suffering from severe mental disorders [23]. Acute bouts of exercise have cognitive and mood-enhancing benefits, including improved executive functioning and lower state anxiety and stress reactivity [24,25]. The mechanisms behind the psychological benefits of exercise in SUDs are not well established, but one tenable hypothesis is that they are partly mediated by changes in the stress hormone cortisol [24].

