Using saliva samples is a noninvasive method for assessing cortisol levels. There is no need for medical staff, and saliva can be stored at room temperature for several hours before freezing. The drawback of saliva cortisol (versus serum cortisol) is that the use of tobacco and the presence of blood in the samples may lead to falsely elevated cortisol levels [50]. To control for this, the laboratory will not analyze samples with traces of blood. Samples with cortisol levels above reference levels will be excluded from analysis.

Dropout rates from treatment studies of SUDs are often high [6,28]. To minimize the risk of dropout, a member of the research group visited the treatment center 1 week before the study to answer questions. The recruitment took place a maximum of two weeks ahead of the trial. We tried to minimize dropout by keeping the overall intervention period short and integrating the interventions into the usual treatment routines at the treatment centers. This also minimized interference in the patients’ usual treatment.

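### The planned repeated-measures ANOVA needs complete records, so excluded or unreturned questionnaires and missed sessions discard ratings that were collected; a mixed model would keep them

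*Protocol article*

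**What the plan says.** All of the following is in the Protocol article.

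- **Analysis** (Statistical Analyses and Power Calculation): change over time is tested with a repeated-measures ANOVA, described as mixed, with group and time as factors, followed by post hoc contrasts.
- **Missing data** (same section): "Due to the experimental study design and the inclusion of only inpatients, we anticipate minimal missing data". Missing items on returned questionnaires are filled by last observation carried forward. If more than half of a returned form is blank, "the questionnaire will be excluded from the analysis".
- **Design** (Study Design and Randomization; Baseline and Follow-up Assessments): a crossover in which each patient attends three sessions and gives five ratings per session, one before and four after.
- **Sources of loss**: under Exclusion Criteria the article reports that some patients relapsed during treatment, and adds: "Patients who were suspected to be under the influence of drugs were asked to discontinue". The Introduction states that "dropout rates from in-patient treatment is around 30" per cent, and the Discussion that "Dropout rates from treatment studies of SUDs are often high".
- **Size**: "we estimate needing at least 21 participants to test our hypotheses"; 39 took part (Results).

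**The concern.** The two missing-data rules do not close the gaps that matter for this analysis. Carrying forward acts within a returned form. It does nothing for a form never handed in or a session not attended, and the half-blank rule removes whole forms. The primary outcome gets limited help, because the Feeling Scale is a single item. If the half-blank rule is applied scale by scale, a blank Feeling Scale is wholly missing and is excluded. If it is applied to the whole set of forms, an answered mood item can be lost because other scales were left blank.

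Classical repeated-measures ANOVA cannot use a record with a hole, so each gap also removes ratings that were obtained. How many depends on how the record is defined:

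- **Literal group-by-time reading:** the record is one session. A gap removes that session's other four ratings, and a missed session removes nothing else.
- **Condition within patient, as the crossover calls for:** the record is the patient. A gap removes all 15 ratings on that outcome, including sessions finished before a discontinuation.

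At stake are precision and the population to which the result applies, since the patients analysed would be those without gaps.

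**Working it through.** **1. The plan's own figure.** The stated inputs are: "Assuming an effect size of 0.3 and power (β) of .8, with 3 groups and 5 measurement points". Alpha, the correlation between repeated ratings (ρ) and the nonsphericity correction (ε) are not given; I assumed 0.05, 0.5 and 1, and read 0.3 as Cohen's f. For the within-between interaction with k = 3 groups and m = 5 times:

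- λ = f²·N·m·ε/(1−ρ), df1 = (k−1)(m−1)ε, df2 = (N−k)(m−1)ε
- N = 21: λ = 0.09 × 21 × 5/0.5 = 18.9, df 8 and 72, power 0.856
- N = 18: λ = 16.2, df 8 and 60, power 0.776

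The stated 21 reproduces, as three separate groups of 7.

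**2. Size of the data set.** 3 sessions × 5 ratings = 15 ratings per patient per outcome. 39 × 3 = 117 sessions and 39 × 15 = 585 ratings.

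**3. Independent loss of single ratings.** The article gives no rate, so p per rating is an assumption. Share of complete sessions = (1−p)^5; share of complete patients = (1−p)^15.

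| p | Ratings observed of 585 | Complete sessions of 117 | Observed ratings discarded (session record) | Complete patients of 39 | Observed ratings discarded (patient record) |
|---|---|---|---|---|---|
| 2% | 573 | 105.8 (90%) | 45 | 28.8 (74%) | 141 |
| 3% | 567 | 100.5 (86%) | 65 | 24.7 (63%) | 197 |
| 5% | 556 | 90.5 (77%) | 103 | 18.1 (46%) | 285 |

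Discarded ratings = observed ratings minus those in complete records. For p = 5% with the patient as record: 556 − 15 × 18.07 = 285.

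**4. Approximate interval widening against no missing data**, 1/√(share complete):

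- Session record: 1/√0.904 = 1.05, 1/√0.859 = 1.08, 1/√0.774 = 1.14
- Patient record: 1/√0.739 = 1.16, 1/√0.633 = 1.26, 1/√0.463 = 1.47

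**5. Clustered loss, patient as record.**

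- 5% lost as whole sessions: 39 × 0.95³ = 33.4 complete patients, widening 1/√0.857 = 1.08
- 5% lost as whole patients: 39 × 0.95 = 37.1
- 10% to 20% of patients discontinuing before their last session (assumed): 39 × 0.10 = 3.9 to 39 × 0.20 = 7.8, so 4 to 8 patients lose any sessions they had finished. On the literal reading those sessions are kept.
- 30% of patients lost outright: 39 × 0.70 = 27.3

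**The case against.** - **The article does not say that a patient is deleted for one gap.** A reader might infer that every hole costs all 15 ratings. On the text as written it costs four, and a missed session costs no other rating. The larger loss appears only when the analysis follows the crossover. This stands, so both cases must be shown.
- **Eighteen complete patients is not a shortfall against 21.** That inference is tempting but not like for like: 21 reproduces for three separate groups of 7, whereas 18 crossover patients would each supply all three conditions. The comparison should not be made.
- **The article's 30% does not refute its expectation.** A reader might see a contradiction. The figure concerns dropout from inpatient treatment, with no time window, whereas the trial is three mornings in one week. The Discussion lists recruitment close to the trial, a visit beforehand, a short period and integration into routine care; Adherence adds on-site reminders. What remains is a tension: inpatient status is offered as reassurance in a document that reports considerable dropout among inpatients.
- **Independent loss is an unfavourable pattern.** Discontinuation and missed sessions are clustered, and clustered loss spoils fewer records (step 5). This stands.
- **Details of missing-data handling may sit in a fuller plan.** True for rules not mentioned. But the ANOVA, the exclusion rule and the expectation are all stated here, and the ANOVA is the part that discards data.

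**Conclusion.** The point holds as a matter of efficiency and of who is analysed. The named analysis, combined with the half-blank rule and a fill-in rule limited to returned forms, discards ratings that were collected. Under an assumed 2% to 5% loss per rating, 90% to 77% of sessions stay complete on the literal reading. With condition within patient, about 29 to 18 of 39 patients stay complete under independent loss, and about 33 if 5% are lost as whole sessions. The rates and the loss pattern are assumptions, because the article gives neither.

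A reader might go further and infer that the treatment contrast is biased because relapsing patients drop out of the analysis. The article does not support that: it gives no number of discontinuations, and nothing links them to the mood contrast between conditions. The narrower analysed population is a real consequence; bias is not demonstrated.

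**What to change.** In Statistical Analyses and Power Calculation, replace the repeated-measures ANOVA with a linear mixed model fitted by REML: fixed effects for condition, period, time and condition × time, and random effects for patient and for session within patient. Use every observed rating of every randomised patient, and keep sessions completed before a discontinuation. Report the observed amount of missing data, by condition and time point, in place of the expectation that it will be minimal.

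The cost is a change of wording and a little more programming. Data collection was already complete when the article appeared, so trial conduct is untouched. The downside is reliance on missing at random; one simple sensitivity analysis, for example assigning less favourable mood values to ratings missing after a discontinuation, would probe it.
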